## Abstract

**Background:**

Alcohol use and anxiety disorders commonly co-occur, resulting in a more severe clinical presentation and poorer response to treatment. Research has shown that approach bias modification (ApBM) and interpretation bias modification (IBM) cognitive retraining interventions can be efficacious adjunctive treatments that improve outcomes for alcohol use and social anxiety, respectively. However, the acceptability, feasibility, and clinical utility of combining ApBM and IBM programs to optimize treatments among comorbid samples are unknown. It is also unclear whether integrating ApBM and IBM *within* each training session or alternating them *between* each session is more acceptable and efficacious.

**Objective:**

This paper describes the protocol for a randomized controlled pilot trial investigating the feasibility, acceptability, and preliminary efficacy of the *Re-train Your Brain* intervention—an adjunct web-based ApBM+IBM program—among a clinical sample of emerging adults with hazardous alcohol use and social anxiety.

**Methods:**

The study involves a three-arm randomized controlled pilot trial in which treatment-seeking emerging adults (18-30 years) with co-occurring hazardous alcohol use and social anxiety will be individually randomized to receive the *Re-train Your Brain integrated* program, delivered with 10 biweekly sessions focusing on *both* social anxiety and alcohol each week, plus treatment as usual (TAU; ie, the model of care provided in accordance with standard practice at their service; n=30); the *Re-train Your Brain alternating* program, delivered with 10 biweekly sessions focusing on social anxiety one week and alcohol the next week, plus TAU (n=30); or TAU only (n=30). Primary outcomes include feasibility (uptake, follow-up rates, treatment adherence, attrition, and adverse events) and acceptability (system usability, client satisfaction, user experience, and training format preference). Secondary efficacy outcomes include changes in alcohol approach and interpretation biases, social anxiety, and alcohol use (eg, drinks per day, binge drinking, drinking motives, severity of dependence, and cravings). The primary end point will be posttreatment (6 weeks postbaseline), with a secondary end point at 3 months postbaseline. Descriptive statistics will be conducted for primary outcomes, whereas intention-to-treat, multilevel mixed effects analysis for repeated measures will be performed for secondary outcomes.

**Results:**

This study is funded from 2019 to 2023 by Australian Rotary Health. Recruitment is expected to be completed by mid-2022 to late 2022, with follow-ups completed by early 2023.

**Conclusions:**

This study will be the first to evaluate whether an ApBM+IBM program is acceptable to treatment-seeking, emerging adults and whether it can be feasibly delivered via the web, in settings where it will ultimately be used (eg, at home). The findings will broaden our understanding of the types of programs that emerging adults will engage with and whether the program may be an efficacious treatment option for this comorbidity.

**Trial Registration:**

Australian New Zealand Clinical Trials Registry ACTRN12620001273976; https://www.anzctr.org.au/Trial/Registration/TrialReview.aspx?id=364131

**International Registered Report Identifier (IRRID):**

PRR1-10.2196/28667

## Introduction

### Background

Social anxiety and alcohol use disorders are highly prevalent [1] and frequently co-occur [2,3]. When they are comorbid with one another, the presenting symptoms tend to be more severe and associated with greater functional impairment than either disorder in isolation [4,5]. This is likely because of the existence of a bidirectional, self-perpetuating cycle, whereby ongoing interactions between the disorders serve to maintain or exacerbate symptoms of both conditions [4,6,7]. The co-occurrence of social anxiety and alcohol use disorders can also interfere with treatment and recovery, with evidence from clinical trials showing that standard single-disorder treatments are less effective for people with comorbid anxiety and alcohol use [4,8-11].

Given the frequent co-occurrence of these disorders and the additional complications that this comorbidity confers on the individual (eg, physical and psychological health, relationships, work, and education) and society (eg, social and economic costs) [4,5,12], it is essential to understand and modify factors that contribute to the maintenance of these conditions. One such factor is implicit or automatically activated cognitive biases. Although there are a variety of implicit cognitive biases associated with social anxiety and alcohol use disorders, two of the most common are alcohol *approach biases* (ie, the tendency for alcohol cues to induce an automatic and habitual approach action [13,14]) and *interpretation biases* (ie, the tendency to interpret ambiguous stimuli, scenarios, and events in a negative manner [15-17]). Alcohol approach biases have been shown to contribute to heavy drinking and predict future alcohol use among adults with an alcohol use disorder [14] and have also been associated with relapse to alcohol following treatment [18,19]. Interpretation biases have been linked to the development of anxiety symptoms and disorders, and the maintenance and severity of these conditions [20,21].

Over the past two decades, several computer-based cognitive training paradigms, known as cognitive bias modification (CBM), have been developed to reduce symptoms by modifying a range of maladaptive implicit biases, including alcohol approach and anxiety-related interpretation biases. *Approach bias modification* (ApBM) is one of the most common types of CBM programs trialed as an adjunctive treatment for alcohol use disorders. It seeks to train adaptive alcohol-avoidance tendencies by getting an individual to repeatedly push away images of alcohol shown on a computer screen. *Interpretation bias modification* (IBM) is one of the dominant CBM programs for ameliorating anxiety symptoms, particularly social anxiety. IBM directly targets negative interpretation biases by repeatedly presenting individuals with emotionally ambiguous social scenarios and training them to resolve the uncertainty in a positive or neutral (vs threatening) way [22]. Several large randomized controlled trials (RCTs) among clinical samples show particularly promising findings for ApBM and IBM interventions, especially in instances where they are added as an adjunct to standard evidence-based treatments, such as cognitive behavioral therapy (as described in detail later) [23-28]. It is argued that this is likely because clients in treatment are typically motivated to change their thoughts and behaviors, which may be a prerequisite for successful training effects [29]. By adding CBM on top of conventional treatment approaches, treatment not only is able to target conscious, deliberate, and explicit negative thinking styles and behavioral responses but can also target unhealthy habitual and implicit processes [30-32]. Thus, a combination of these complementary approaches further aids in the effectiveness of treatment on clinical outcomes. In contrast, there has been mixed empirical support for the efficacy of ApBM and IBM programs as stand-alone interventions among nonclinical samples (eg, heavy drinking university students) [29,33,34]. Meta-analyses that synthesize findings on efficacy from a mixture of clinical and nonclinical studies have produced similar inconclusive findings [34,35], perhaps as a result of the substantial heterogeneity in study samples, designs, and methodologies [29,36].

Several large RCTs [23-26] and reviews [29,37,38] have provided evidence in support of the beneficial effects of ApBM when delivered to clinical samples in conjunction with standard treatments. Notably, 3 studies in Germany showed that the provision of 4-12 sessions of ApBM alongside treatment as usual (TAU; eg, inpatient alcohol use treatment or abstinence-oriented cognitive behavioral therapy) to alcohol-dependent adults was associated with significantly lower alcohol consumption and 7%-13% reduced rates of relapse one year later compared with patients who received TAU plus a sham placebo training or TAU only [23,24,26]. One of these studies reported that the change in alcohol approach biases mediated the change in relapse rates and a stronger approach bias at baseline moderated ApBM effects [24], whereas another was unable to replicate these effects [26]. Furthermore, a recent multisite RCT conducted in Australia reported significant improvements in abstinence rates among those given four sessions of ApBM during inpatient detoxification (54%), relative to sham control training (42%) [39]. A significant reduction in approach bias was observed among those in ApBM but not in the sham-training condition after training. Overall, ApBM has shown fairly consistent promising effects in clinical contexts and has since been added to German and (forthcoming) Australian guidelines for treating alcohol-related disorders [40,41].

Clinical studies investigating the efficacy of IBM have shown that training can promote the development of a positive interpretive bias in socially anxious populations and that these modifications are associated with reductions in social anxiety symptoms [27,28]. Although there are fewer clinical RCTs in number relative to ApBM, one study in the United States found that adults diagnosed with generalized social anxiety disorder who received 12 sessions of IBM experienced significantly greater reductions in negative interpretations of ambiguous scenarios, self-reported and clinician-rated social anxiety symptoms, and rates of social anxiety disorder diagnosis (65% vs 13%) from pre- to postassessment, relative to a sham control-training condition. Moreover, the effects on social anxiety were sustained at the 3-month follow-up [27]. Similarly, a pilot study found that the provision of four IBM sessions combined with CBM for attentional biases to an outpatient sample diagnosed with social or generalized anxiety disorder was associated with significant reductions in both types of cognitive bias and state and trait anxiety [28]. Studies investigating the mechanism of change for these effects have reported that negative interpretation biases mediated the relationship between the training group and improvement in social anxiety symptoms [27]. These findings are also supported by a recent review of meta-analyses and a systematic review and meta-analysis of CBM programs for anxiety, which both concluded that single- or multisession IBM training among clinically diagnosed and subclinical samples can significantly reduce threat-related interpretation biases [42] and reduce anxiety levels compared with a sham training or waitlist control condition [43].

A limitation to the clinical utility of ApBM and IBM interventions to date is that they have predominantly been restricted to the confines of a laboratory or clinic [44]. Despite this, internet delivery is a promising option for increasing the scalability and sustainability of these interventions. A handful of published studies evaluating the effectiveness of web-based ApBM and IBM have indicated that there is promise in this mode of delivery; however, additional studies are required to make more definitive conclusions regarding their efficacy. For instance, two studies in Europe provided evidence that web-based IBM training can significantly shift interpretations from negative to positive [45,46], with one study showing clinically significant improvement in social anxiety symptoms (eg, 48% of participants no longer met criteria for social anxiety disorder after eight IBM sessions) [46]. Another study found that four sessions of web-based ApBM among nontreatment-seeking problem drinkers were associated with improved drinking outcomes across three active intervention groups; however, this effect was also evident in the sham control-training group [47]. The authors highlight that despite their null findings, integrating web-based ApBM with more traditional cognitive and motivational interventions may be key to improving results and call for further research that combines these supplementary treatments. It is apparent that there is a need for more studies of web-based CBM programs (particularly ApBM) with clinical populations where there is a motivation to change their thoughts and/or behaviors.

Overall, although the evidence base for the efficacy of laboratory- and web-based ApBM and IBM is accumulating for adults with singular disorders, their efficacy when delivered to people with co-occurring social anxiety and alcohol use problems remains largely unknown. To the authors’ knowledge, only one RCT exists that examines the efficacy of an attention bias–focused CBM program among a socially anxious, alcohol-dependent adult sample (N=86) [48]. The findings indicated that there were significant reductions in attentional biases, alcohol use disorder, and social anxiety symptoms in both the intervention and control groups; however, no significant between-group differences were identified for any symptom measures. Given the interconnections between anxiety and alcohol use problems and the likely coexistence of approach and interpretation biases, a promising avenue that has not been explored is the potential of combining existing effective ApBM and IBM cognitive retraining protocols to optimize standard treatments among comorbid anxiety-alcohol samples. Moreover, given the peak onset and disability associated with anxiety and alcohol use disorders occurs between adolescence and early adulthood [49,50], the provision of a comorbidity-focused ApBM+IBM training program at an earlier age (and earlier in the course of their disorder) represents a promising opportunity to intervene before problems become chronic and entrenched in adulthood.

Addressing these gaps in the literature, the research team codeveloped a hybrid, web-based ApBM+IBM for emerging adults with co-occurring hazardous alcohol use and social anxiety (*Re-train Your Brain*), as a supplement to TAU for anxiety and/or alcohol use. As trial repetition, boredom, and disengagement are serious concerns for CBM training [28], it deemed was important to assess attitudes toward this treatment and adapt the program where necessary. In line with this, a study was conducted to evaluate the acceptability of a beta version of the *Re-train Your Brain* program according to the perspectives of clinicians and emerging adults with hazardous drinking and heightened social anxiety [51]. The results indicated that the ApBM+IBM intervention was an acceptable adjunct to traditional evidence-based treatments with potential clinical utility, a finding that mirrors previous CBM acceptability studies [52,53]. To enhance engagement, clinical utility, and intrinsic motivation to complete the training, clinicians and emerging adults suggested that the program should include a psychoeducational and motivation enhancement-type module before the first training session. In light of the aforementioned issues surrounding boredom and disengagement from CBM programs, it was considered possible that the format in which the ApBM+IBM program is delivered might influence engagement and outcomes. For instance, one delivery option could be to integrate the ApBM and IBM components into each training session (50:50 ratio) to provide variation in tasks *within* each training session and reduce boredom. This may, in turn, result in better retention, engagement, and outcomes because of a shorter time being spent completing each repetitious task. An integrated variation might also be especially beneficial because it gives people practice shifting multiple cognitive processes close in time, which likely better mimics the cognitive flexibility needed in daily life (where a cue may require both healthy alcohol-avoidance reactions and healthy interpretation bias in a short space of time) as compared with more temporally distant application of modified cognitive processes. It is equally possible, however, that doing shorter bursts of the two types of training within each session may water down any potential clinical effects. Another option could be to alternate the ApBM and IBM training *between* sessions, thereby providing full-length sessions of each type of training, although fewer in number to achieve the same treatment dose. Clinicians and emerging adults were asked to rate the format they perceived would be most preferable to end users of the program: (1) an *integrated* program that combines shortened versions of both ApBM and IBM within each training session or (2) an *alternating* program that provides ApBM in one training session and IBM in the next, in an alternating pattern. The results indicated that there was no consistent preference for the program format (8/15, 53% vs 7/15, 47% for integrated and alternating, respectively), and further research is required to better understand the impact of training format on acceptability and efficacy outcomes. Overall, the beta *Re-train Your Brain* ApBM+IBM program was well received, and obtaining feedback from service providers and emerging adults was critical to ensuring that the program was age-appropriate, engaging, and potentially useful for end users. However, to date, no research has been conducted to evaluate the feasibility of delivering this program, whether it is deemed acceptable by people who complete the training, and how efficacious it is in reducing the targeted cognitive biases, hazardous drinking, and social anxiety symptoms.

### Aims

This paper describes the study protocol for a randomized controlled pilot trial investigating the feasibility, acceptability, and preliminary efficacy of the *Re-train Your Brain* intervention—a web-based hybrid ApBM+IBM program—as an adjunct to TAU for anxiety and/or alcohol use, compared with TAU only, among emerging adults with co-occurring hazardous alcohol use and social anxiety disorder symptoms. The *Re-train Your Brain* program will be delivered in two formats (integrated or alternating) to ascertain which is preferred by emerging adults and whether one shows more promising signs of efficacy.

It is hypothesized that the integrated and alternating *Re-train Your Brain* ApBM+IBM programs will both be feasible to implement and deemed acceptable by emerging adults. It is hypothesized that the integrated format will be rated as more acceptable and engaging than the alternating format because of the variation of tasks *within* each session (ie, less time will be spent on each task within each session, which may reduce boredom and disengagement often experienced because of the repetitive nature of each task). Although this is a pilot trial that is not powered to detect clinically significant group-by-time interaction effects, based on previous research, it is likely that both the integrated and alternating *Re-train Your Brain* programs will result in trend improvements in cognitive biases, anxiety, and alcohol-related outcomes, relative to the control condition. It is further hypothesized that greater effect sizes will be observed in the integrated *Re-train Your Brain* intervention group than in the alternating intervention group because of greater levels of engagement with the program. The results will be used to inform the design and power analysis of a future definitive trial.

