##### Acceptability

Measures of acceptability and usability of the program will be assessed at postintervention (6-week postbaseline). *The usability of the program* will be assessed using the 10-item System Usability Scale [68]. Items are rated on a 5-point Likert scale ranging from 1 (*strongly disagree*) to 5 (*strongly agree*). The scores for each item are converted to a new number, ranging from 0 to 4. A total score is then computed by summing the converted item scores and multiplying this by 2.5, giving a range of 0 to 100. Higher values denote greater usability and higher satisfaction with the program. Cut-off scores using a *school grade analogue* have recently been suggested for interpreting the scores (F=0-51.7; D=51.8-62.6; C=62.7-72.5; B=72.6-78.8; and A=78.9-100), with a score over 68 being considered above average [69]. *Satisfaction* with the program will be measured by Client Satisfaction Questionnaire-8 [70]. Items are rated on a 4-point Likert scale from 1 to 4, with total scores ranging from 8 to 32. Higher scores indicate greater client satisfaction. Acceptability will also be assessed by 13 acceptability items (eg, how user-friendly, simple to use, logical, and engaging the tasks were), rated using a 5-point Likert scale from 0 (*not at all*) to 4 (*very*). The survey will also contain several open-ended questions about the most or least helpful and enjoyable features of the program. To determine *which intervention delivery model is preferred*, participants in the active intervention groups will complete four user experience questions after completing each of the *Re-train Your Brain* sessions. The four items will assess their motivation while training, how much they enjoyed the training, how much they liked the delivery format, and whether they found the training simple and user-friendly, using a 5-point Likert scale (from 0 *not at all* to 4 *extremely*).

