### Statistical Analysis and Power Calculations

As this is a pilot trial, a formal power calculation is not required [81,82]. The pilot trial is essential to determine the expected size of effect, which will be used to inform the sample size of a future definitive RCT aiming to assess the efficacy of the *Re-train Your Brain* program. Rates of attrition will be used to indicate estimated follow-up rates in future trials. On the basis of several rules of thumb used to determine an appropriate sample size for a pilot study [83-85], a sample size of 90 young people (30 per arm) was selected to provide sufficient data on the feasibility, acceptability, and preliminary efficacy of the program, although we recognize that the scope of this pilot trial does not allow for a fully powered test of efficacy. Data will be collated and analyzed using StataCorp data analysis software [86].

Descriptive statistics for primary and secondary outcomes will be conducted based on frequencies and cross-tabulations. Analyses for secondary (preliminary) efficacy outcomes will use multilevel mixed effects analysis for repeated measures, which is a flexible analytic approach for modeling change over time using RCT data [87,88]. All models will use baseline measurements as the reference point to estimate participant-specific starting points and change over time. The intervention condition will be represented by a dummy-coded variable, and the condition by time interaction will be examined to assess between-group differences in outcomes over time. Analyses will be consistent with an intention-to-treat framework, with all randomized participants included in the analysis models, regardless of training completion or loss to follow-up. Missing data will be accommodated in these models using maximum likelihood estimation. Preliminary models will be estimated, with model fit statistics examined to determine the most appropriate model and covariance structure. Cohen *d* will be calculated from model-estimated marginal means and SEs to determine the size of the effect between conditions at the relevant end point. In addition, effect sizes will be analyzed as a function of session completion (ie, completion of six or more training sessions, given that this has been identified as the mean optimum number of ApBM sessions in past research [67]).

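### The hypothesis that the integrated format is more acceptable than the alternating one concerns a primary outcome, but the plan gives that outcome only descriptive statistics, with no between-format difference and no interval

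*Protocol article*

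**What the plan says.** The Aims section explains that the program is delivered in two formats "to ascertain which is preferred by emerging adults", and states the expected direction: "It is hypothesized that the integrated format will be rated as more acceptable and engaging than the alternating format". The abstract lists among the primary outcomes "acceptability (system usability, client satisfaction, user experience, and training format preference". The Acceptability section specifies the SUS (0 to 100), the CSQ-8 (8 to 32) and four user experience items answered after every session in the two active arms. Those four items are what is to determine the preferred delivery model.

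The abstract divides the analyses by type of outcome: "Descriptive statistics will be conducted for primary outcomes, whereas intention-to-treat, multilevel mixed effects analysis for repeated measures will be performed for secondary outcomes". The section on statistical analysis and power repeats the division. For description it says "Descriptive statistics for primary and secondary outcomes will be conducted based on frequencies and cross-tabulations". For modelling it says "Analyses for secondary (preliminary) efficacy outcomes will use multilevel mixed effects analysis for repeated measures". The condition-by-time contrast and Cohen d are described as part of that modelling.

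**The concern.** Whether each format is acceptable is a question that description can answer. Whether one randomized format is rated higher than the other is a comparison, and it needs an estimated difference with some statement of precision. It is the only comparative hypothesis on a primary outcome: the remaining hypotheses in the Aims either concern both formats without comparing them or concern secondary efficacy outcomes. Each participant trains in one format only, so preference too has to be read from a contrast between arms.

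The result has uses. The Aims say the findings will inform the design of a definitive trial, and the control group is later to be offered the format that participants prefer. The earlier acceptability study ended at 8/15 against 7/15, with no consistent preference. Without an interval, this trial could leave the same ambiguity, or a chance gap could be taken as support for or against the hypothesis.

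**Working it through.** **Inputs from the protocol article.** 30 participants per arm, so 60 in the format comparison. SUS range 0 to 100. The Strengths and Limitations section cites 34.2% attrition for web-based interventions in general; this is not a planning value for the trial.

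**Assumptions.** Responders per arm n = 30 (everyone answers) down to n = 20, since 30 × (1 − 0.342) = 19.7. SUS SD of 12.5 to 20; the article gives none.

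**The plan's own figure.** 3 × 30 = 90 agrees with the stated total. It rests on rules of thumb for pilots, without alpha, power, SD or effect size, so there is no formula to reproduce.

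**Precision of the format difference.** In SD units, SE = √(2/n) and the 95% half-width = t(0.975, 2n − 2) × SE.

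| n per arm | SE (SD units) | Half-width (SD units) | SUS points, SD 12.5 | SUS points, SD 20 |
|---|---|---|---|---|
| 30 | √(2/30) = 0.258 | 0.517 | 6.5 | 10.3 |
| 20 | √(2/20) = 0.316 | 0.640 | 8.0 | 12.8 |

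**How often chance alone produces a gap.** With no true difference, P(|observed gap| ≥ d) = 2 × [1 − Φ(d/SE)].

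| Gap d | n = 30 per arm | n = 20 per arm |
|---|---|---|
| 0.2 SD | 44% | 53% |
| 0.3 SD | 25% | 34% |
| 0.5 SD | 5% | 11% |

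For d = 0.3 the ratios d/SE are 0.3/0.258 = 1.16 and 0.3/0.316 = 0.95.

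**Direction alone.** With no true difference the integrated format comes out ahead in about half of trials. If its true advantage is 0.3 SD, it still comes out behind in Φ(−1.16) = 12% of trials at 30 per arm and Φ(−0.95) = 17% at 20.

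The results in SD units apply to any per-participant score, including the CSQ-8 total, taken on its own SD.

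**The case against.** Descriptive analysis of acceptability is normal in a pilot, and no power calculation is needed. A cross-tabulation by arm already sets the formats side by side for categorical items, and nothing forbids arm means, SDs or intervals for the totals. Interval wording is the kind of detail that a condensed article may leave to an analysis plan that is not shown.

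Much of this stands, and it limits the point to the missing contrast and its precision. It does not remove it. The article is not silent: it says in two places what primary outcomes receive, and in both it reserves model-based comparison for secondary outcomes. Its admissions of low power concern group-by-time effects and efficacy, not the acceptability comparison.

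Three stronger readings are tempting and are not supported:

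- A reader might infer that the hypothesis will be settled by the raw difference. No decision rule is stated, so this is only what could happen if nothing is added.
- A reader might infer that the arms will be compared by SUS letter grade, since the Acceptability section prints the bands "F=0-51.7; D=51.8-62.6; C=62.7-72.5; B=72.6-78.8; and A=78.9-100". It offers them for interpreting scores and says nothing of comparing arms by them. How often two equal arms would fall in different grades also depends heavily on where the true mean lies relative to a cut-off.
- A reader might bring in session completion. The article classes it under feasibility, and the quoted hypothesis is about ratings.

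**Conclusion.** The point holds in limited form. A directional between-format hypothesis on a primary outcome is paired with an analysis that specifies neither the difference nor its uncertainty. With 20 to 30 responders per arm the 95% half-width would be about 0.64 to 0.52 SD, or 6.5 to 12.8 SUS points if the SD is 12.5 to 20. A gap of 0.3 SD or more would arise by chance in about 25% to 34% of trials. Large gaps are a different matter: 0.5 SD arises by chance in only 5% to 11%. The responder numbers and the SDs are assumptions. The mismatch in the text does not depend on them. The trial can run unchanged; what suffers is the interpretation of the format comparison.

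**What to change.** In the section on statistical analysis and power, and in matching words in the abstract, state that:

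- the integrated-minus-alternating difference will be reported with its 95% confidence interval for the SUS total, the CSQ-8 total and the four post-session items, using a repeated-measures model over sessions for the last;
- this comparison is exploratory;
- the format hypothesis will be interpreted from the range of differences that the interval does not exclude, and not from the raw direction.

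A rule that declares one format better only when an interval excludes zero is not advised. There is no lead measure, and at a true difference of 0.3 SD the power would be only 21% with 30 per arm and 16% with 20. Such a rule would put a weak confirmatory test into a pilot.

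The cost is a sentence or two of wording and a few lines of Stata, with no new data. The downside is that the format conclusion will often have to be stated as uncertain.
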